## Abstract

**Background:**

Cardiometabolic diseases are highly prevalent in Aotearoa New Zealand. Dietary intake is a modifiable risk factor for such diseases and certain dietary patterns, specifically the Mediterranean diet (MedDiet), are associated with improved metabolic health. This study aims to test whether an intervention including a Mediterranean dietary pattern incorporating high quality New Zealand foods (NZMedDiet pattern) and behavior change science can improve the metabolic health of participants and their household/whānau.

**Methods and analysis:**

This is a multi-center, three-stage trial with two parallel group superiority randomized controlled trials (RCTs), and a longitudinal cohort study embedded within the trial design. The first RCT (RCT 1) is a comparison of the NZMedDiet pattern compared to usual diet for 12 weeks. The Behavior Change Wheel was used to select and implement strategies to support participant adherence to the NZMedDiet, such as web-based nutrition education on healthy shopping and cooking. The second (RCT 2) compares online social support to no online social support for 12 weeks, administered to participants immediately following RCT 1. The third stage is a longitudinal cohort study where all participants are followed from the beginning of their start of the active intervention for 12 months in total. The primary outcome measure for each stage is the metabolic syndrome severity score (MetSSS). The duration of enrolment is 12–15 months. The total recruitment target is 200 index participants and their household/whānau members who participate with them, and the primary analyses will be intention to treat on index participants.

**Discussion:**

The trial will test whether the NZMedDiet pattern and behavior change support improves the cardiometabolic health of people in Aotearoa New Zealand.

**Clinical trial registration:**

https://www.anzctr.org.au/Default.aspx, identifier ACTRN12622000906752 and https://www.isrctn.com/, identifier ISRCTN89011056 (Spirit 2).

## Introduction (Spirit 6a)

Cardiometabolic diseases, including type 2 diabetes (T2DM) and cardiovascular disease, are common. In 2017, one in three deaths were caused by cardiovascular disease in Aotearoa New Zealand (1). Diet is an important modifiable risk factor for cardiovascular disease (2), and certain dietary patterns such as the Mediterranean diet (MedDiet) are associated with a reduced risk of cardiometabolic disease (3, 4). The MedDiet is rich in minimally processed plant-based foods and legumes; low in saturated fat and red meat; and a distinguishing feature is its use of olive oil (3). Nutrition knowledge regarding the benefits of adopting a dietary pattern such as the MedDiet does not always translate into a change in dietary behavior. Dietary change can be affected by barriers to behavior change such as cost, acceptability, time, dietary knowledge, nutrition competence and cultural practices (5).

Recent research from our group, and others, reports that the use of, and adherence to, a MedDiet pattern in Aotearoa New Zealand is low (6, 7). To promote a MedDiet pattern in countries such as Aotearoa New Zealand, attention should be given to optimizing a dietary intervention, taking into consideration the behavioral and social structures that decrease barriers to adherence (8, 9). Studies of interventions aimed at improving dietary patterns in community living individuals report that barriers to a healthier diet include the “good taste” of unhealthy food, inconvenience and difficulties in enjoying non-fatty food (5, 10). Individual choice, cultural norms and taste preferences of the study population are important to consider when adapting a dietary pattern into a population. Studies recruiting Māori, who are indigenous New Zealanders, and young adults of various ethnicities, report that the provision of meal preparation support and financial assistance for the use of healthy diets, may be useful to support changes in dietary patterns (11, 12). Food provision, barriers to which may have otherwise prevented dietary change, such as the lack of prior exposure, uncertainty about how to prepare the food, and cost, is a potential intervention that may enable the uptake of a healthier diet (13). The social context of sharing and consuming meals within a household/whānau is an important aspect of many cultures and takes into consideration that all the household/whānau members within a dietary intervention may facilitate ongoing dietary change for all (12, 14, 15). The provision of food and related education is reported to support adherence to a healthy diet, and lower the burden associated with food preparation, particularly when applied on a household/whānau basis (16). The behavior change wheel framework is underpinned by the Capability, Opportunity and Motivation Behavior (COM-B) theory and facilitates consideration of the aforementioned barriers to adopting the desired dietary pattern (17, 18). Consequently, this framework will be used to identify effective and feasible strategies to overcome these and support participant adherence.

The primary objective of this trial is to evaluate if a Mediterranean dietary pattern incorporating high quality New Zealand foods (NZ MedDiet pattern), delivered in a household/whānau setting and underpinned by behavior science can improve the cardiometabolic health of people in Aotearoa New Zealand. We have chosen to do this through the metabolic syndrome severity score (MetSSS). The metabolic syndrome (MetS) refers to the clustering of several risk factors including hypertension, obesity, dyslipidemia and insulin resistance, which identifies individuals at greater risk of CVD and T2DM (19). MetS is commonly classified in a dichotomous fashion, as having or not having MetS. An alternative approach, which gives a continuous and more nuanced description, is the Metabolic Syndrome Severity Score (MetSSS) which quantifies the value of MetS latent factors for an individual, and the resulting score behaves like a Z-score in that it is normally distributed in a population. The MetSSS has been shown to predict future cardiometabolic disease and can be modified by diet, exercise, and pharmacological intervention to estimate change in cardiometabolic disease risk, and is therefore a useful tool in assessing the impact of a dietary intervention (19). It has been validated in a New Zealand population and has been shown to be responsive to diet and lifestyle interventions in people with pre-diabetes (19–21).

A secondary objective of this study is to evaluate the effectiveness of continued online social support (Spirit 7).

## Methods and analysis

This protocol is reported in accordance with the SPIRIT (Standard Protocol Items: Recommendations for Interventional Trials) guidance (22). In preparation for this trial, a feasibility study was conducted to test the recruitment and screening strategy, retention, acceptability of the method of delivery of a component of the intervention, and to collect relevant data to refine the power calculation for this study (23).

### Trial design (Spirit 8)

This is a multi-center, three-stage trial, with two randomized controlled trials (RCTs); both parallel group superiority trials, and a longitudinal cohort study. The first RCT (RCT 1) compares the effect of Mediterranean dietary pattern incorporating high quality New Zealand foods (NZMedDiet pattern) to usual diet on MetSSS, a marker of cardiometabolic health for 12-weeks. The intervention in RCT 1 includes elements of behavior change science including the provision of food, recipes, weekly meal plans, access to web-based nutrition education and opt-in online social support. From here on within the manuscript ‘RCT 1 intervention’ is referred to as a package including these described aspects. The second RCT (RCT 2) compares the opt-in online social support, to no online social support with an outcome assessment 12 weeks after the second randomization (Figure 1). Those participants who were originally randomized to the control group in RCT 1 will be given the RCT 1 intervention before the second randomization. After the second randomization, both groups continue to have access to the bespoke study website housing nutrition information and education. The third stage is a longitudinal cohort study where all participants are followed for 12 months from the start of the dietary intervention. The trial design is summarized in Figure 1 (Spirit 8).

**Figure 1 fig1:**
[figure not shown]
Study design.

### Trial setting (Spirit 9)

The trial settings are four centers in Aotearoa New Zealand: two based at university research units (University of Auckland and University of Otago, Christchurch), one at a community-based traditional Māori meeting place (Tū Kotahi Māori Asthma and Research Trust at Kōkiri Marae in Lower Hutt, Wellington), and the other based at a hospital-based research unit (the Center for Endocrine Diabetes and Obesity Research (CEDOR) in Wellington).

### Eligibility criteria (Spirit 10)

Index participants and their household/whānau members will be recruited through the four trial sites. Multiple recruitment strategies will be used to recruit participants to the study. Advertising to the public through television, newspaper and radio advertisements, study posters, study information sessions, and other hardcopy and online media, including targeted social media, and institutional mailing lists will be used. Participants will be recruited from the local populations of the area of each study center. An important element of recruitment for research in Aotearoa New Zealand is to enhance Māori capacity and capability for research, and to include Māori and their whānau as research participants. This will be enabled by the close relationship between CEDOR and Kōkiri Marae to support the staff at Kōkiri Marae and oversee the running of the trial at that site (Figure 2).

**Figure 2 fig2:**
[figure not shown]
Formulae used for the calculation of the MetSSS.

Tables 1, 2 show the eligibility criteria for both index participants and household/whānau participants. Screening will occur consistent with our feasibility study (23). Potential participants who respond to advertisements or who otherwise contact researchers will be directed to the trial website^1^ and an on-line questionnaire to complete as step one of the two step screening process. The website provides information about the trial and the questionnaire includes contact information and questions to enable calculation of the AUSDRISK (24). If this score is greater than 12, potential participants will be invited to a second step of screening which is conducted in-person at one of the study sites. This will include a fasting blood sample and anthropometric measurements to enable the calculation of the MetSSS. If they have a fasted MetSSS greater than 0.35, they will be the index participant. Once identified, and having given written consent for participating, household/whānau members of the index participant will also be invited to participate in the trial. Between one and five household/whānau members per index participant will be invited. The food provision intervention (see below) will be calculated based on the total number of people in the household, for up to 6 members. All household/whānau members who qualify for inclusion will complete age-appropriate questionnaires (Table 3), will be invited to undertake clinical measurements and to provide blood samples if aged 11 years and over. If an index participant and household/whānau participant were to separate over the course of the trial, attempts would be made to gather data from those who continue living in the same building as the index participant.

**Table 1 tab1:** Inclusion and exclusion criteria for index participants.

Inclusion criteria	Exclusion criteria
18–70 years	Previous bariatric surgery, or pre-existing Type 1, or Type 2 diabetes. Where a previous diagnosis of T2DM is uncertain, this will be defined as ever having had two consecutive HbA1c results ≥50 mmol/mol that are at least three months apart
Metabolic syndrome severity Score (MetSSS) >0.35	Total cholesterol ≥8 mmol/L
1–5 household/whānau members agree to participate*	Chronic severe renal disease (eGFR <30 mL/min/1.72m^2^)
Participants and their whānau are planning to live together for the duration of the study	Current pregnancy or breastfeeding, or planning to conceive during the study (due to impact on interpreting outcome measures)
Access to the internet at home	Unstable body weight (active weight loss/gain >5 kg in prior three months)
Able and willing to attend all site visits	Gastrointestinal disorder that alters the digestion and absorption of nutrients (e.g., ulcerative colitis, Crohn’s disease, coeliac disease, an ileostomy or colostomy).
Willing to adhere to local health and safety regulations	Severe food allergies (anaphylaxis) in any household/whānau member
For the consumer insights study, there needs to be a willingness to be interviewed	Medication use – current use of medications that modify blood sugar levels, or anticipated regular use of oral or injected steroids
	Does not agree to refrain from donating blood for three months prior to each study visit (due to impact on HbA1c)
	Is participating in, or has recently participated in another research study involving an intervention which may alter outcomes of interest to this study
	Any other condition or situation, which in the view of investigators would affect the compliance or safety of the individual taking part

^*^Additional whānau/household members, if they are eligible and interested, may also be enrolled as an index participant.

**Table 2 tab2:** Inclusion criteria for household/whānau participants and exclusion criteria for household/whānau participants who provide a blood sample.

Living in the same household as the index individual	Age ≤ 11 years
Consent/assent to consume the intervention food	Pre-existing Type 1 diabetes.
	Chronic severe renal disease (eGFR <30 mL/min/1.72m^2^)
	Current pregnancy or breastfeeding, or planning to conceive during the study (due to impact on interpreting outcome measures)
	Unstable body weight (active weight loss/gain >5 kg in prior three months)
	Gastrointestinal disorder that alters the digestion and absorption of nutrients (e.g., ulcerative colitis, Crohn’s disease, coeliac disease, an ileostomy or colostomy).
	Medication use – current use of medications that modify blood sugar levels, or anticipated regular use of oral or injected steroids
	Does not agree to refrain from donating blood for three months prior to each study visit (due to impact on HbA1c)
	Is participating in, or has recently participated in another research study involving an intervention which may alter outcomes of interest to this study
	Any other condition or situation, which in the view of investigators would affect the compliance or safety of the individual taking part
	Children living in the household but who do not have a legal guardian also living in the household

**Table 3 tab3:** Summary of questionnaires.

	How administered	What it measures	Which participants
Otago short-form FFQ (25)	On REDCap	Habitual dietary intake	All index participants and household/whānau participants aged 11y and over
Three factor eating questionnaire or child version (26)	Emailed survey which will be linked to REDCap	Cognitive restraint uncontrolled eating and emotional eating	All index participants and household/whānau participants aged 11y and over
24 h Food recall	On intake 24 website (https://intake24.co.uk/info/recall)	Dietary intake in previous 24 h	All index participants and household/whānau participants aged 11y and over
IPAQ Physical activity (27)	On REDCap	Habitual physical activity	All index participants and household/whānau participants aged 11y and over
SF 36 (28)	On REDCap	Quality of life	All index participants and household/whānau participants aged 11y and over
Kaupapa Māori Wellbeing questionnaire	On REDCap	Covering the four realms of Te Whare Tapa Whā to determine quality of life from a Māori perspective	Any Māori participants aged 11y and over
Gastrointestinal symptom rating scale (29)	On REDCap	Gastrointestinal symptoms	All index participants and household/whānau participants aged 11y and over
Self-evaluation COM Questionnaire (30)	On REDCap	Evaluates the process; assesses participant perceptions of barriers and enablers throughout the study to see if the behavior change support is working as it is intended	Index participants
Impact Evaluation for Nutrition and Behavior Change Support (31)	On REDCap	Assesses how the behavior change support impacts participants (including engagement, satisfaction, and perception of impact)	Index participants

FFQ, food frequency questionnaire; IPAQ, international physical activity questionnaire; COM, capability opportunity motivation.

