### Assignment of interventions

#### Allocation sequence generation in RCT 1 and in RCT 2 (Spirit 16a)

Index participants and their household/whānau will be block randomized into RCT 1 at site level to either start the intervention package or continue usual dietary intake for 12 weeks. If there is a second person within the household/whānau who meets the criteria for an index participant, they will be allocated to the same arm as the first index participant, where applicable. Index participants will be randomized using a computer-generated sequence. Household/whānau members will be randomized to the same arm as their corresponding index participant. Index and household/whānau participants will all be randomized once their data have been collected at Visit 2. It is not possible to blind index participants or their household/whānau members to the intervention in RCT 1. Nor is it practical to blind study staff collecting data, however the principal investigator, study statistician and the laboratory team will remain blinded throughout the study and analysis period. Participants will be informed of which arm of RCT 2 they are randomized to after they have completed the RCT 1 intervention.

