#### Plan to promote participant retention and complete follow-up (Spirit 18b)

If randomized to the intervention, participants may opt out of intervention activities that are offered but remain enrolled in the study and continue with clinical assessments, complete questionnaires and allow researchers access to their medical records. Index and household/whānau participants will receive phone, text message or email reminders regularly to complete the questionnaires, depending on their preference.

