### Statistical analyses

The primary analysis will be conducted according to the intention to treat principle. Appropriate data descriptions and plots will be used for all variables. Change from baseline variables will also be described as paired differences but, in general, baseline values of response variables will be used as covariates in analyses rather than analyzing change from baseline. For RCT 1 and RCT 2 and for the index participants, the primary analysis for the primary outcome variable will be Analysis of Covariance (ANCOVA) with the baseline value of the MetSSS as a continuous covariate and the randomized treatment as the main explanatory variable. This strategy will also be used for all continuous outcome variables with the appropriate baseline value of any specific outcome variable as the covariate. The baseline measurement will be just before the relevant randomization. Normal distribution assumptions for residuals will be checked for models of continuous outcome variables and if these are badly violated transformations, such as a logarithm transformation, will be used. For some variables, outlined in Table 4, it is already established that the logarithm transformation is likely to be appropriate. Where appropriate transformations cannot be identified a rank-based procedure, the Mann–Whitney test with the Hodges-Lehmann estimator of location difference, will be used. For the primary outcome variable, the MetSSS, a sensitivity analysis will be a secondary analysis adjusting for possible confounding by important explanatory variables that may have not been evenly distributed by the randomization. These will be as a composite categorical variable for whether medication was changed for any of blood pressure control, glucose management, or lipid control; and separately, for physical activity assessed by the international physical activity questionnaire score. Analysis will be by ANCOVA with these confounding variables in addition to the baseline MetSSS and randomized treatment. Another secondary analysis will be to explore if randomized treatment allocation is associated with different effects in subgroups; using an appropriate treatment by subgroup interaction models. These subgroups are: age, sex, baseline diet adherence score, household size, and whether a household has children. For the continuous variables the analysis of the interaction will be on the continuous scale but for illustrative purposes, and for use in a Forest-like plot, will also be estimated for the first and third quartile of the continuous predictor distribution. Another important secondary analysis will be of all participants treating each household as a cluster and using a Mixed Linear model with baseline measurement and randomized treatment as fixed effects, and household clusters as random effects. If in the event there are very few clusters, the random effect may not be estimable and then this will be equivalent to ANCOVA. The Intraclass correlation coefficient for the clustering effect will be estimated directly from the variance components in the mixed linear models, should a cluster effect be estimable. Categorical and ordinal variables will be analyzed by logistic regression, the latter corresponding to ordinal regression, for the individual participant analysis, and by a Generalized Mixed Linear Model for all participants. There may be other effect modifiers that we will consider but these will be outlined in the Statistical Analysis Plan.

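### After a household separates, the protocol seeks data from members still in the index participant's building and makes no provision for randomised members who are not, which leaves the secondary household analyses open to selection

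*Protocol article*

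**What the plan says.** Under Allocation sequence generation, household members are part of the randomised population: "Household/whānau members will be randomized to the same arm as their corresponding index participant". The timing is also fixed there: "Index and household/whānau participants will all be randomized once their data have been collected at Visit 2". The footnote to Table 5 has them attend visits 2, 3a/3b, 4 and 5. The two outcome sections (RCT 1 and RCT 2; longitudinal cohort study) give them secondary outcomes at every stage.

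The rule on separation is the last sentence of the text under Eligibility criteria (Spirit 10) that precedes Table 1: "attempts would be made to gather data from those who continue living in the same building as the index participant". No other sentence deals with members who move away, or with an index participant who moves away from them.

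Under Statistical analyses, the household data have a named use: "Another important secondary analysis will be of all participants treating each household as a cluster". Intention to treat is stated for the primary analysis: "The primary analysis will be conducted according to the intention to treat principle". The abstract gives its population: "the primary analyses will be intention to treat on index participants".

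For people who stop taking part in the intervention, the retention section (Spirit 18b) sets a different rule: "participants may opt out of intervention activities that are offered but remain enrolled in the study and continue with clinical assessments".

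**The concern.** Because randomisation follows Visit 2, a household separation during the trial is normally a post-randomisation event. If outcomes are sought from members who still share the index participant's building and not from others, the members measured at later visits are selected by that event. Separation may be related to health, to household circumstances or to the arm, since the intervention is built around shared meals. Read literally, if the index participant moves out alone, no remaining member is covered, even one who received the whole food package.

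At stake are the all-participant mixed model and the household secondary outcomes. These bear on a stated aim, because the abstract asks about the metabolic health of household members as well as of participants. The rule concerns data collection, so a later analysis plan cannot repair it: outcomes that were never sought cannot be recovered.

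**Working it through.** The protocol gives no separation rate and no sample size for household members, so it has no figure of its own to reproduce here. Its 184 is a calculation for index participants and plays no part.

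**Comparison of the rules**

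| Situation after randomisation | What the protocol provides | Place |
|---|---|---|
| Participant opts out of intervention activities | Stays enrolled, assessments continue | Retention (Spirit 18b) |
| Household member still in the index participant's building after a separation | Data are sought | Eligibility criteria (Spirit 10) |
| Household member no longer in that building | Nothing stated | – |

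The first and third rows can describe the same loss of exposure to study food. Only the first has a follow-up rule, and no reason is given for the difference. In a model with baseline as covariate and one later outcome, a member with no later measurement contributes nothing to the treatment comparison.

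**Illustration of size, on assumed inputs**

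- Effect in members who stay, τ_S = 0.4 MetSSS units. This is the design difference in the Sample size section, set for index participants and borrowed here.
- Effect in members who leave, τ_L = 0 to 0.2 (assumed).
- Share separating before the outcome visit, s = 1% to 10%, equal in both arms (assumed).

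Effect in all randomised members = (1 − s)·τ_S + s·τ_L.

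Overstatement when only stayers are measured = τ_S − [(1 − s)·τ_S + s·τ_L] = s·(τ_S − τ_L).

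| s | τ_L = 0.2 | τ_L = 0 |
|---|---|---|
| 1% | 0.01 × 0.2 = 0.002 | 0.01 × 0.4 = 0.004 |
| 2% | 0.02 × 0.2 = 0.004 | 0.02 × 0.4 = 0.008 |
| 5% | 0.05 × 0.2 = 0.01 | 0.05 × 0.4 = 0.02 |
| 10% | 0.10 × 0.2 = 0.02 | 0.10 × 0.4 = 0.04 |

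Even the largest entry is a tenth of the assumed effect (0.04/0.4). Separation that differs by arm, or that depends on health differently in the two arms, could add bias in either direction. The documents give no basis for putting a number on that.

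**The case against.** The strongest reply is that the sentence is permissive. It names people to be pursued and does not say that others are dropped, withdrawn or excluded. Reminders under Spirit 18b go to index and household participants with no condition on where they live, and withdrawal under Spirit 11b is the participant's own choice. Data gathered before a separation are not said to be discarded. All of this stands, so a reader should not infer an exclusion rule or count members as removed by it. What remains is that the sentence singles out one group and leaves the other without provision. Its natural reading is that movers are not pursued.

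A reader might also infer that an intention-to-treat promise is broken. It is not. The principle is stated for the primary analysis, and that analysis is on index participants. The possible exception is a second index participant in the same household (allowed by the footnote to Table 1) who moves out, since the sentence does not say how that person is treated.

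A third tempting reading is that controls, followed to week 64 and not week 52, are exposed to the rule for longer. The timeline in Table 5 does not support this for any stated randomised comparison:

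- RCT 1 is assessed at week 12 in both arms.
- RCT 2 spans 24 − 12 = 12 weeks in the early-start group and 36 − 24 = 12 weeks in the delayed-start group.
- The cohort endpoint is 52 weeks after the intervention starts in both groups (52 − 0 and 64 − 12).

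The extra control weeks may thin the delayed-start group before its intervention begins, but they do not make follow-up unequal between randomised arms.

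Finally, planned co-residence for the whole study is an entry criterion in Table 1, so separations should be uncommon. Living with the index participant is also an inclusion criterion for household members, so interest in co-resident members is partly a choice of target population. That supports a co-resident analysis as an addition, but not leaving the follow-up of other randomised members unstated.

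**Conclusion.** The concern holds as a weakness in a data-collection rule that affects secondary analyses. On its natural reading, the separation sentence makes outcome collection for randomised household members depend on a post-randomisation event, contrary to the principle that the protocol applies to people who stop the intervention. The all-participant mixed model and the household secondary outcomes may therefore be subject to selection. The primary index-participant analysis is generally untouched, and the protocol does not contradict itself.

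The effect is probably small: 0.002 to 0.04 MetSSS units across the illustrated range. That range rests on assumed separation rates, assumed effects in leavers, a borrowed design effect and equal separation by arm. The correction is still worth making, because it is cheap now and missing outcomes cannot be obtained afterwards.

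**What to change.** Amend the separation sentence under Eligibility criteria so that outcome data are sought at every scheduled visit from all randomised index and household participants, wherever they live. Where a site visit is not feasible, collect at least the questionnaires remotely. Record the date of separation. Under Statistical analyses, state that members are analysed in their allocated arm and in the household to which they belonged at randomisation, and make an analysis restricted to co-resident members supportive. The wording should also cover a second index participant who moves out.

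The cost is one amended sentence, one added data field, and modest extra contact and visit effort for the few members who move. Some of their clinical measurements and fasting bloods may still be missing, since these are taken at the research sites. Food provision and the intervention itself do not change.
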